**5. Study design**

*5.1 Design*

We will conduct a clinical trial in which we monitor patient-generated health data from 500 patients discharged from one of the University of Pennsylvania Health System hospitals for 6 months. Patients will be randomly assigned to track their data using a smartphone app (which collects step counts) or a wearable activity tracker (which collects step counts and sleep patterns/duration). There will be no intervention for either group, both are being passively monitored. The group assigned to use the smartphone app will receive a wearable activity tracker at the end of the 6 month study.

The University of Pennsylvania Health System will help us to design a real-time list of patient admitted to the hospitals that fit our inclusion criteria. Research coordinators will visit these patients to describe the study and assess their interest in participating. Research coordinators will help all interested participants to create an account on the Way to Health online research platform to begin the enrollment process.

All patients will complete several validated surveys including the Medical Outcome Study (MOS) Social Support, DOSPERT risk preferences, Morisky Medication Adherence (MMAS-8), the Big Five personality test, and short form of the International Physical Activity Questionnaire (IPAQ).

Patients will complete informed consent to allow us to access their health insurance claims data from Independence Blue Cross (IBC), Pennsylvania Health Care Cost Containment Council (PHC4), New Jersey Department of Health, and CVS, their electronic health record data (inpatient and outpatient) from the University of Pennsylvania Health System, their financial data (credit score and timeliness to pay bills) from the University of Pennsylvania Health System or a credit vender, and patient-generated health data collected by their smartphone or wearable activity tracking device.

*5.2 Study duration*

The study period is 6 months in duration. The randomized controlled trial is expected to take about 12 months to complete enrollment with 6 months of follow-up data collection. Analysis is then expected to take about 6 months to complete after data from third parties are received.

*5.3 Target population*

The study population will be drawn from patients admitted to the Hospital of the University of Pennsylvania or Penn Presbyterian Medical Center.

*5.4 Accrual*

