**9. Analysis plan**

We will conduct preliminary descriptive analyses to compare univariate associations between levels and changes in levels of patient-generated health data and health care utilization.

A standard model will be developed using inpatient claims data by fitting a multivariate logistic regression model to each of the binary dependent outcome variables using hospital and time fixed effects (month and year), and including independent variables for patient demographics, comorbidities, and length of stay in the hospital.

An enhanced model will be developed using the design of the standard model but also incorporating independent variables that represent data on medication adherence, from the electronic medical record on clinical, social, and behavioral factors, from validated surveys, and data from activity tracking devices.

We will perform tests between the enhanced (using data from smartphones and wearables) and standard models to identify significant predicators of the outcome measures that will inform the final model. We will also compare the cross-validated c-statistic between the standard and enhanced models using the replication method. To validate the final model, we will randomly split the participants in several cohorts (e.g. 5 samples of 100 participants) and using all one cohort to validate and the others to train the model. We will perform this several times until each cohort has been used to validate the model. We will evaluate the c-statistic using the replication method.

We will compare predictors of the outcomes and the cross-validated c-statistics between the final model for participants using smartphones compare to participants using wearable devices using the replication method.

All hypothesis tests will be 2-sided and use a significance level of P < 0.05.

The study analysis and prediction models will be informed by another retrospective study that has already been approved by the University of Pennsylvania Institutional Review Board (Protocol # 824908).

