An enhanced model will be developed using the design of the standard model but also incorporating independent variables that represent data on medication adherence, from the electronic medical record on clinical, social, and behavioral factors, from validated surveys, and data from activity tracking devices.

We will perform tests between the enhanced (using data from smartphones and wearables) and standard models to identify significant predicators of the outcome measures that will inform the final model. We will also compare the cross-validated c-statistic between the standard and enhanced models using the replication method. To validate the final model, we will randomly split the participants in several cohorts (e.g. 5 samples of 100 participants) and using all one cohort to validate and the others to train the model. We will perform this several times until each cohort has been used to validate the model. We will evaluate the c-statistic using the replication method.

We will compare predictors of the outcomes and the cross-validated c-statistics between the final model for participants using smartphones compare to participants using wearable devices using the replication method.

All hypothesis tests will be 2-sided and use a significance level of P < 0.05.

The study analysis and prediction models will be informed by another retrospective study that has already been approved by the University of Pennsylvania Institutional Review Board (Protocol # 824908).

Final Statistical Analysis Plan

We will conduct preliminary descriptive analyses to compare univariate associations between levels and changes in levels of patient-generated health data and health care utilization.

A standard model will be developed using inpatient claims data by fitting a multivariate logistic regression model to each of the binary dependent outcome variables using hospital and time fixed effects (month and year), and including independent variables for patient demographics, comorbidities, and length of stay in the hospital.

An enhanced model will be developed using the design of the standard model but also incorporating independent variables that represent data on medication adherence, from the electronic medical record on clinical, social, and behavioral factors, from validated surveys, and data from activity tracking devices.

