We will perform tests between the enhanced (using data from smartphones and wearables) and standard models to identify significant predicators of the outcome measures that will inform the final model. We will also compare the cross-validated c-statistic between the standard and enhanced models using the replication method. To validate the final model, we will randomly split the participants in several cohorts (e.g. 5 samples of 100 participants) and using all one cohort to validate and the others to train the model. We will perform this several times until each cohort has been used to validate the model. We will evaluate the c-statistic using the replication method.

We will compare predictors of the outcomes and the cross-validated c-statistics between the final model for participants using smartphones compare to participants using wearable devices using the replication method.

All hypothesis tests will be 2-sided and use a significance level of P < 0.05.

The study analysis and prediction models will be informed by another retrospective study that has already been approved by the University of Pennsylvania Institutional Review Board (Protocol # 824908).

Statistical Analysis Plan Summary of Changes

None

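### On its natural reading, the plan picks the final model's predictors by significance test before cross-validating that model on the same participants, so the final model's c-statistic will be optimistic

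*Supplement*

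**What the plan says.** The Final SAP, repeated in Final Protocol section 9, sets out five steps in this order.

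1. It defines the enhanced model: "An enhanced model will be developed using the design of the standard model but also incorporating independent variables that represent data on medication adherence", followed by medical-record, survey and activity-device variables. No selection rule and no number of variables is given.
2. Tests between the enhanced and standard models are used "to identify significant predicators of the outcome measures that will inform the final model". The only criterion is the general one: "All hypothesis tests will be 2-sided and use a significance level of P < 0.05".
3. The analysis will "compare the cross-validated c-statistic between the standard and enhanced models using the replication method". The selected final model is not named here.
4. The final model is validated: "To validate the final model, we will randomly split the participants in several cohorts (e.g. 5 samples of 100 participants"), "using all one cohort to validate and the others to train the model", rotating until every cohort has served for validation.
5. The last comparison concerns "the cross-validated c-statistics between the final model for participants using smartphones compare to participants using wearable devices".

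Protocol section 5.1 gives the sample size: "we monitor patient-generated health data from 500 patients discharged". The SAP closes by saying that the models will also be informed by a separate retrospective study, without saying how.

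**The concern.** Cross-validation estimates performance in new patients only if the held-out cohort played no part in building the model. Here the object being validated is the final model, and step 2 has already shaped it using outcome tests. If those tests used the participants who are later split into cohorts, refitting the coefficients in each training set does not undo the choice of variables. A noise variable that happened to correlate with readmission in the full sample will tend to do so in the validation cohorts too, because they are part of that sample.

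Protocol section 2 makes the prediction algorithm the objective of the study, so an inflated c-statistic would misstate how well the study's main product works. Section 4 puts existing models at 0.60-0.70. Against that range, an error of a few hundredths is material.

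**Working it through.** The documents give no target c-statistic, power or planned event count, so there is no figure of the plan's to reproduce beyond 5 × 100 = 500, which agrees with section 5.1.

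**Inputs from the documents.** n = 500; two-sided 0.05; five cohorts of 100; background 30-day readmission of about 1 in 5 and existing c-statistics of 0.60-0.70 (section 4).

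**Assumptions.** 20% events, which is a background figure for patients with chronic conditions and not a planning value; 10, 20 or 40 added candidates; all added candidates independent normal noise; selection by Wald P < 0.05 in the enhanced model; 250 per arm (1:1 allocation), with selection done within the arm. The replication method is not defined, so a DeLong-type test stands in for it.

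**Events.** 500 × 0.20 = 100 in total; 400 × 0.20 = 80 per training set; 100 × 0.20 = 20 per validation cohort; 250 × 0.20 = 50 per arm.

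**Chance selections.** The expected number is 0.05 × k and the chance of at least one is 1 − 0.95^k. For k = 10, 20, 40 this gives 0.5, 1 and 2 variables, and 40%, 64% and 87%.

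**Simulation A** (five true standard predictors; 400 data sets per column; n = 500, 20% events). Optimism is the cross-validated c after one-time selection minus the same model's c in new patients.

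| | 10 | 20 | 40 |
|---|---|---|---|
| Selected once on all, then cross-validated | 0.634 | 0.639 | 0.651 |
| True c of that model in new patients | 0.633 | 0.627 | 0.614 |
| **Optimism** | **0.001** | **0.012** | **0.037** |
| Selection repeated in each training set | 0.621 | 0.612 | 0.599 |
| Full enhanced model, no selection | 0.605 | 0.590 | 0.571 |
| Standard model | 0.627 | 0.626 | 0.625 |

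Two further settings (300 data sets each, 20 candidates) gave optimism of 0.023 at n = 500 with 10% events and 0.028 at n = 250 with 20% events.

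**Simulation B** (standard c about 0.65, 20% events, two separate runs):

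| | 10 | 20 | 40 |
|---|---|---|---|
| n = 500 | 0.014 | 0.025-0.027 | 0.046-0.051 |
| n = 250 | 0.025 | 0.046-0.049 | 0.085-0.086 |

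With 40 candidates at n = 500, one run of B returned a cross-validated 0.670 for a model whose true c was 0.670 − 0.051 = 0.619. That is below the 0.647 of the standard score alone, so the apparent gain was really a loss.

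**Check on the remedy.** Nested selection came within about 0.01 of true performance in B. In A it was 0.012 to 0.015 below (0.621 − 0.633, 0.612 − 0.627, 0.599 − 0.614). It errs slightly on the cautious side. With only 10 candidates in A, the one-time selection was the closer of the two.

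**The case against.** **Selection on all 500 is an inference.** The SAP does not say which data the tests use, and it says they inform the final model, not that they determine it. The tests might be block tests and not variable-by-variable screening. The retrospective study could in principle supply the predictor choice from outside. All of this stands as a limit on certainty. It does not remove the concern. No hold-out or nesting is described, the use made of the retrospective study is not stated, and the surveys and device data are described only as collected in this trial.

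**The size may be negligible.** This stands for about 10 candidates. Five surveys plus medical-record, adherence and device variables make 20 to 40 plausible, but the plan gives no count.

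**The enhanced-versus-standard test.** A reader might infer that this test is also biased towards the enhanced model. The text does not support that. It compares the standard model with the enhanced model containing all added sources, not with the selected final model. If the full model is refitted in each fold, no selection leaks and overfitting counts against it. In A it scored 0.605, 0.590 and 0.571 against about 0.626, and won at P < 0.05 in at most 0.3% of runs. In B it scored 0.620, 0.603 and 0.578 against about 0.65. Bias in its favour would arise only if the compared model had been screened on the outcome in the same data, for example through the preliminary univariate analyses. The plan neither states this nor rules it out. In that case A gives false wins of 2.8%, 6.8% and 19.5%, against a nominal 2.5%.

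**The device comparison.** Both arms carry optimism, so a bias in their difference does not follow automatically. If selection were done by arm, the sleep variables would give the wearable arm more candidates. In B at n = 250, 30 against 20 candidates gave 0.065 against 0.049, a difference of 0.016. This is conditional, because the plan does not say whether selection is done by arm.

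**Conclusion.** The point holds for the final model's own cross-validated c-statistic and for the arm-specific values. As naturally read, the plan validates an already selected model on the participants who selected it.

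With 20% events and pure-noise additions, optimism is about 0.00-0.01 (10 candidates), 0.01-0.03 (20) and 0.04-0.05 (40) at n = 500. It is about 0.03-0.05 with 20 candidates in an arm of 250, if allocation is 1:1 and selection is done within the arm. These figures rest on assumed candidate counts, an assumed event rate, independent predictors and Wald screening.

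The point does not extend to the enhanced-versus-standard comparison as the SAP words it. Nor do the documents name a c-statistic as the primary result: section 3.1 names 30-day readmission as the primary outcome and goes no further.

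**What to change.** Replace the validation wording in the SAP and in Protocol section 9 with:

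> All steps that use the outcome (predictor testing, selection, tuning, choice of the final model) are repeated from scratch inside each set of training cohorts, separately within each arm for arm-specific models, or are done only on separate data such as the retrospective study. The held-out cohort is used only to score the resulting model.

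Also state that the enhanced model in the enhanced-versus-standard comparison is the pre-specified full model, or one whose selection is nested in the same way. Define the replication method.

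Full-sample tests may still be reported to describe predictors.

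If intervals come from a bootstrap, keep all copies of a patient in the same fold. In a null check with 40 noise candidates, properly nested selection gave enhanced minus standard of −0.031. Bootstrapping with ordinary fold assignment gave +0.020 on average, because copies of a patient fell on both sides of the split.

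The cost is SAP wording, some computing time and a less favourable reported c-statistic. No data collection changes.
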